**11 References 21**

**List of abbreviations**

ALC, alternate level of care

CI, cognitive impairment

HAFD, hospital-associated functional decline

TCP, transitional care program

TCU, transitional care unit

BI, Barthel Index

OASIS Walking Intervention, Older Adults with cognitive impairment performing sit to stands and Walking in transitional care programs Intervention

PI, Principal Investigator

RA, Research Assistant

SDM, Substitute Decision-Maker

Client Satisfaction Questionnaire, CSQ

**Protocol Summary**

**The OASIS Walking Study - Older Adults with cognitive impairment performing SIt to Stands and Walking in a transitional care unit: a feasibility Study**

**Sample size**: n = 26 patient participants and their SDM (Total 52).

**Study population**: older adults ≥65 years admitted to one of two facility-based TCUs

**Study design**: A feasibility study using a quasi-experimental one-group repeated measures design will be conducted.

**Study duration**: December 2023-July 2024

**Study objectives**: The proposed study has two objectives:

1) To determine the feasibility of and satisfaction with the OASIS Walking Intervention in older adults with CI in two facility-based TCUs.

2) To determine the efficacy of the OASIS Walking Intervention on older adults’ muscle strength, mobility, functional status, quality of life, and discharge destination.

**Endpoints of the study**: The study is expected have direct value to older adult patients and their care partners. If shown to be efficacious, the study can also decrease care requirements for patients within the TCP and when they return home or when they are discharged to long-term care, which ultimately would be expected to help the health care system. The ultimate goal is to promote continued functioning, mobility, and improved quality of life for older Canadians.

# GENERAL INFORMATION

## Protocol title

The OASIS Walking Study - Older Adults with cognitive impairment performing SIt to Stands and Walking in transitional care programs: A feasibility Study

## Literature review

Cognitive impairment (CI), which can include dementia, delirium, and unspecified CI (1, 2), has a global prevalence of between 5.1% and 41%, and a median of 19.0% (3). For dementia in particular, the number of people living with this condition globally is expected to nearly double from 50 million in the year 2020 to 82 million in 2030, and 152 million in 2050 (4). In Canada, the number is expected to nearly triple from about 600,000 in 2020 to 1.7 million in 2050 (5). In Ontario, the number of people with dementia is anticipated to increase from over 228,000 in 2016 to over 430,000 in 2038 (6).

Older adults (≥65 years) (7) with CI are frequently hospitalized (8), with the most common admitting diagnoses being cerebrovascular disease, heart failure, pneumonia, transient ischemic attack, renal failure, septicemia, pulmonary embolism and urinary tract infections (9). While in hospital, they often experience mobility limitations (10), low activity levels (11), and hospital-associated functional decline (HAFD) (12), that is, the inability to perform usual activities of daily living due to weakness, reduced muscle strength, and reduced exercise capacity, which occurs due to bedrest, deconditioning, and acute illness during hospitalization (13).

Many of these older adults with CI who experience HAFD are subsequently transferred to facility-based transitional care programs (TCPs), which are short-term, post-acute care facilities that provide low-intensity restorative care (7). In Ontario, facility-based TCPs have been created for patients with a prolonged hospital length of stay who are labelled as Alternate Level of Care (ALC) and are unable to be discharged home; many are waiting to be discharged to a nursing home post hospitalization (14) and many experience a decline in their ability to perform activities of daily living (ADLs) (15). However, in a systematic review led by the interventionist for this present study (16), it was found that older adults with CI in facility-based TCPs experience worse outcomes than those without CI. While those with CI did improve in functional status in eight of 13 studies, a greater percentage of participants without CI experienced functional improvement compared to those with CI; as well, gains in functional status were smaller for older adults with CI compared to those without CI (16). These results suggest the need for additional supports and interventions to improve outcomes. Moreover, a smaller percentage of older adults with CI were discharged home post TCP, compared to those without CI (16). Given the growing number of older adults with CI, there is an urgent need for interventions in the TCP setting to improve outcomes for this population.

Older adults often experience HAFD (13, 17, 18), with a recent meta-analysis reporting a 30% prevalence of HAFD among hospitalized older adults (18). HAFD is problematic as it can have serious consequences for the health of older adults with CI. HAFD can lead to not only decreased mood and quality of life (19), but also to pressure injuries, falls, increased morbidity, and mortality (20). Moreover, HAFD can lead to rehospitalization, increased health care costs, and institutionalization (20).

HAFD can be explained by the pathophysiology of functional decline as described by the Cascade to Dependency (21) and functional decline secondary to muscle disuse models (22). Together, these models explain that aging-related factors (reduced muscle strength and aerobic capacity) combine with hazards of hospitalization (such as bedrails and tethers that promote immobility, inactivity, and bedrest) to result in disuse-induced functional decline (21, 22). Disuse-induced functional decline is characterized by muscle atrophy, loss of muscle strength, and functional deterioration, all of which increase the risk for admission to a nursing home (21, 22). Muscle atrophy occurs because of an imbalance between muscle protein synthesis and breakdown (22). During physical inactivity, the body is in a pro-inflammatory state, which is thought to lead to the activation of skeletal muscle proteolytic pathways (pathways which break down skeletal muscles) and a suppression of anabolic signaling pathways (pathways which promote the creation of muscle) (22).

To counteract the deconditioning and functional decline, there is a need for anabolic strategies (which build muscle) (22). Aerobic activity, such as walking, increases the levels of proteins (heat shock proteins) that facilitate protein synthesis and the repair of damaged proteins (22). Resistance training causes anabolic signaling pathways to be activated through increasing mechanical and metabolic stress and promotes muscle growth through increasing muscle protein synthesis; thus, resistance training such as raising from a chair as fast as possible, which uses the own body as resistance, can greatly increase muscle mass and strength and improve functional ability (22).

**Literature Review**

A comprehensive search of the literature involving mobility interventions led by nurses yielded: zero studies in the TCP setting; six studies with significant results involving older adults with cognitive impairment and walking interventions that were led by nurses or that could be done by nurses in the nursing home setting (23-30); and one study with significant results involving sit to stand activity in the nursing home setting (31).

In nursing homes, walking had a typical dose of 30 minutes per session (24, 25, 28-30), ranged from two (23) to seven (27) sessions per week; and duration ranged from six weeks (28) to six months (29). Overall, the most effective intervention was administered by a nurse and involved 2-4 walking sessions per week for 4 months and incorporated a person-centered communication care plan (23). This study had the highest recruitment and adherence rates, monitored intervention fidelity, and resulted in a significant improvement to all outcomes (functional mobility, activities of daily living function, and quality of life).

One study done in nursing homes involving older adults with dementia found that doing sit to stands 6 sit to stands per day resulted in maintained mobility (measured by the amount of time to perform one sit-to-stand) (p=0.01), which can also be a measure of lower extremity muscle strength (31).

**Gap in the Literature**

To the interventionist’s (AC’s) knowledge, there have been no nurse-led intervention studies done to date which combine sit to stand activity, a walking intervention, and a patient-centered communication care plan for older adults with CI in facility-based TCPs. Given the poorer outcomes for older adults with CI in facility-based TCPs, and the promising findings of sit to stand activity, walking interventions, and person-centered interventions in other inpatient settings, it is expected that a complex intervention which combines these three components will result in improved outcomes.

In order to address this gap in the literature, a feasibility study needs to be undertaken. A feasibility study is designed to assess an intervention, including optimal content, delivery, and adherence to the intervention, as stated in the new framework on complex intervention research that was commissioned by the Medical Research Council (MRC) and the National Institute of Health Research (NIHR) (32). This framework outlines that a feasibility study should be done to test the feasibility of a complex intervention in order to make decisions about progression to the next stage of evaluation (32).

# PURPOSE OF THE STUDY

The purpose of this study is to determine the feasibility of and satisfaction of participants with a novel intervention – the OASIS Walking Intervention (that is, the Older Adults with cognitive impairment performing Sit to Stands and Walking Intervention) in facility-based TCPs.

The second aim is to determine the efficacy of the OASIS Walking intervention on muscle strength, mobility, functional status, quality of life, and discharge destination.

# RESEARCH QUESTIONS

1. What is the feasibility of implementing the OASIS Walking Intervention in community-dwelling older adults with CI in facility-based TCPs, as determined by recruitment rate, retention rate, and adherence?

2. What is the satisfaction of older adults with CI with the OASIS Walking Intervention?

3. Does the OASIS Walking Intervention result in improved muscle strength, mobility, functional status, and quality of life in older adults with CI?

4. What percentage of the participants are discharged home and how many are discharged to the nursing home post intervention?

**Study Hypotheses**

- It is hypothesized that the OASIS Walking Intervention will be feasible as evidenced by a moderate recruitment rate (>50%), high retention rate (≥80%), and high adherence rate (attendance to ≥75% of all intervention sessions) (28).
- It is hypothesized that the participant satisfaction will be high (Client Satisfaction Questionnaire (CSQ) of 3 or more on all CSQ items) (33).
- It is hypothesized that the OASIS Walking Intervention will result in improved muscle strength (reduction in the time to perform one sit to stand by ≥0.87 seconds, p=0.01 (31), mobility (minimum detectable change (MDC) ≥9.1 meters on two-minute walk test (34)), functional ability (≥1 point improvement in Barthel Index (BI) considered as clinically meaningful (35)) in older adults with CI in facility-based TCPs, and quality of life (minimally clinical important difference is an increase in 3 points (36)).

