# STUDY DESIGN

## Overall design

A feasibility study will be undertaken for this three-component intervention project. A feasibility study is in keeping with the MRC and NIHR framework which states that for complex interventions, a feasibility study is done to assess and refine the intervention prior to carrying out a full-scale evaluation (63). In terms of study design, a quasi-experimental one group time series design will be used.

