**Secondary Outcomes**

Efficacy will be assessed using measures for muscle strength, mobility, functional status, quality of life, and discharge destination. The primary outcome for efficacy will be lower extremity **muscle strength**.

**1. Lower extremity muscle strength.** Lower extremity muscle strength will be measured using the time to perform one sit-to-stand (42, 43). Time to perform one sit-to-stand has good validity and reliability. The ability to perform one sit to stand has been used in a study involving sit-to-stand activity with older adults with dementia in nursing homes (31). Repeated observations of the sit to stand test by one observer yielded correlations of 0.89 to 0.96 (44).

Older adults who are frail, such as those who are in nursing homes, must use their arms to stand and may be unable to complete more than one sit to stand (45). For a study involving sit-to-stand activity with older adults with dementia in nursing homes, participants were asked to stand from a seated position three times, with the time to complete the sit to stand measured at the third time using a stopwatch (31, 45) (personal communication with [name] January 16, 2023). Similarly, for the present study, the interventionist or RA will ask participants to stand from a seated position three times, with the time to complete the sit to stand measured at the third time using a stopwatch (Appendix E). The interventionist and the RAs will measure the time to complete the sit to stand for participants until ≥75% interrater agreement is reached (46). Then only one RA or the interventionist will collect the rest of the outcome measures data.

**2. Mobility.** Mobility will be measured using the two-minute walk test (2MWT). The 2MWT has good validity and reliability. It has been used in studies involving older adults with dementia in nursing homes (23, 34). As well, the 2MWT has been shown to provide sufficient data to objectively quantify gait measurements, similar to the six-minute walk test (47). The 2MWT has a test-retest reliability coefficient of 0.98 (0.96–0.99) and an inter-rater reliability of 0.92 (0.86–0.96) when assessed in frail older adults with dementia (34). Distances walked for the 2MWT among older adults with dementia in nursing homes and day care centers ranged between 63.1-63.6 meters (34). The minimal detectable change (MDC), that is, the minimum change that is considered a true change in performance, for the 2MWT is 9.1 meters (34).

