# STATISTICS

**Sample Size**

An activity-based study involving older adults with dementia in the nursing home setting (31) that used time to perform one sit to stand found a moderate effect size (Cohen’s d) of 0.48. Since the present study will use repeated measures ANOVA, a Cohen’s *f* of 0.25 (a suggested value for moderate effect size) (55) was used in the sample size calculation. Based on an *f* of 0.25, a power of 0.8 and an alpha of 0.1, in keeping with those used in a mobility study involving older adults with dementia (23), a sample of 21 participants will be needed for this study. Using an alpha of 0.1 can be acceptable for exploratory or preliminary studies (56) (p. 188). An attrition rate of just under 20% over the course of a 6-week study will be taken into account, as was experienced in a 6-week intervention study involving older adult residents with dementia (28). Thus, a sample of 26 participants will be recruited for this study. G*Power 3.1.9.7 software (57) was used for the sample size calculation for an ANOVA: Repeated measures, within factors statistical test with one group, three measurements, 0.6 for the correlation among repeated measures, and 0.8 for nonsphericity correction (which is a mild departure from sphericity) (56).

The sample size is achievable based on input provided by our collaborating TCP administrators, as the TCP has a 35-bed capacity and most patients have cognitive impairment.

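### The hypothesised sit-to-stand gain of at least 0.87 s is credited to a study that the protocol elsewhere says maintained sit-to-stand time, and the contrast behind the figure is never stated

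*Protocol*

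**What the plan says.** The protocol refers to the nursing-home sit-to-stand study (reference 31) in three places that bear on this point.

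- **Study Hypotheses.** Improved muscle strength is expressed as a "reduction in the time to perform one sit to stand by ≥0.87 seconds, p=0.01 (31").
- **Literature Review.** The same study's sit-to-stand activity "resulted in maintained mobility (measured by the amount of time to perform one sit-to-stand) (p=0.01").
- **Sample Size.** The same study "found a moderate effect size (Cohen’s d) of 0.48". The contrast that this effect size measures is not given.

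Under Secondary Outcomes the protocol states "The primary outcome for efficacy will be lower extremity" muscle strength, and "Lower extremity muscle strength will be measured using the time to perform one sit-to-stand". Under Overall design, "a quasi-experimental one group time series design will be used". The only effect this study can observe is therefore change within participants over T1, T2 and T3. The Plan for Analysis tests that change with repeated measures ANOVA, or Friedman's test if the assumptions fail.

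**The concern.** One study, one measure and one p-value carry two different results. Maintained time means a change from baseline near zero; the hypothesis requires a fall of at least 0.87 s. Either one section misdescribes the source, or 0.87 s is not a change from baseline.

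The second possibility matters because of the design. A finding of maintenance is usually significant only against a group that got worse. If 0.87 s is the gap between the two groups, it has been carried over as a before-after target into a study with no comparator. Participants could then do exactly what the Literature Review describes and still not meet the lead efficacy hypothesis. The study is meant to inform the next stage of evaluation, so its conclusion on this outcome should not depend on a figure whose meaning is unknown.

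The p-value inside the hypothesis adds to the confusion. It is the source study's result, yet placed there it can be read as this study's significance level, while the Sample Size section uses an alpha of 0.1.

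**Working it through.** **1. The protocol's sample size, and whether 0.87 s enters it.** Inputs from Sample Size: f = 0.25, alpha = 0.10, one group, m = 3 measurements, correlation 0.6, nonsphericity 0.8.

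- Noncentrality = f² × n × m × ε / (1 − ρ). At n = 21: 0.0625 × 21 × 3 × 0.8 / 0.4 = 7.875.
- Degrees of freedom: (3 − 1) × 0.8 = 1.6 and (21 − 1) × (3 − 1) × 0.8 = 32.
- Power is 0.811 at n = 21 and 0.792 at n = 20, so 21 reproduces.
- With 19% attrition, 21 / (1 − 0.19) = 25.9, so 26 also reproduces.

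The 0.87 s figure appears nowhere in this calculation, and the sample size is not in error.

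**2. The two descriptions side by side.**

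| | Literature Review | Study Hypotheses |
| --- | --- | --- |
| Source | reference 31 | reference 31 |
| Measure | time for one sit-to-stand | time for one sit-to-stand |
| p-value | 0.01 | 0.01 |
| Result | maintained (change about 0 s) | reduction of at least 0.87 s |

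Read as changes from baseline, the last row differs by 0.87 s.

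**3. What follows if 0.87 s is a between-group difference.** Suppose the true mean change here is 0, as the Literature Review describes. With n = 21 completers and a normal approximation, the chance that the observed mean reduction reaches 0.87 s is 1 − Φ(0.87 / (SD / √21)).

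The protocol gives no SD. Assuming that 0.87 s and d = 0.48 describe the same contrast, the implied SD is 0.87 / 0.48 = 1.81 s.

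- Taken as the SD of change: SE = 1.81 / √21 = 0.396; 0.87 / 0.396 = 2.20; probability 1.4%.
- Taken as the SD of a single timing, with the protocol's correlation of 0.6: SD of change = 1.81 × √(2 × 0.4) = 1.62 s; SE = 0.354; probability 0.7%.

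Because the SD is an assumption, a range is needed:

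| Assumed SD of change (s) | Probability of an observed mean reduction ≥0.87 s when the true change is 0 |
| --- | --- |
| 1 | <0.1% |
| 1.5 | 0.4% |
| 2 | 2.3% |
| 3 | 9.2% |
| 4 | 16% |

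**4. If 0.87 s is instead a true within-person reduction.** The observed mean then reaches it with probability 50%, whatever the SD. In that case the target is correctly sourced and the wording to correct is in the Literature Review.

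**The case against.** **The figure decides nothing formally.** It appears once, in a hypothesis. The ANOVA, the sample size and the primary feasibility outcomes do not use it. This stands: a reader might infer that the study would fail a success criterion, but no such decision rule exists. What is at stake is whether the stated efficacy hypothesis is met.

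**The between-group origin is an inference.** This also stands. A reader might conclude that the source merely maintained function and that 0.87 s is therefore wrong. The Literature Review does not say that nothing better than maintenance was seen, and the protocol does not name the contrast. If the source reported a within-group reduction of 0.87 s, the consequence in step 3 of the working falls away.

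**Aiming higher than the source is legitimate.** The source study averaged six sit-to-stands a day. This intervention sets larger targets in weeks 4 to 6 and adds walking and a communication care plan. That is a fair reason to expect more than maintenance, and doing so is no error. It does not explain why 0.87 s with p=0.01 is credited to a study described as showing maintenance.

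**Comparison with measurement error.** The protocol reports that "Repeated observations of the sit to stand test by one observer yielded correlations of 0.89 to 0.96", and for the two-minute walk it uses "the minimum change that is considered a true change in performance, for the 2MWT is 9.1 meters". A reader might infer that 0.87 s is too small to be a real change: with an SD of 1.81 s and those correlations used as reliabilities, one person's 95% minimal detectable change is 1.96 × √2 × 1.81 × √(1 − r), or 1.67 to 1.00 s. The documents do not support that criticism. The correlations come from a different source, the SD is assumed, and a group mean can shift reliably by less than one person's detectable change. Nor does the protocol claim a common standard for its four thresholds.

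**Conclusion.** The protocol contradicts itself on what the source study showed for its lead efficacy outcome, and as written 0.87 s is not supported as a change-from-baseline target. The contradiction rests on the text alone. Which section is wrong cannot be settled without the source.

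The size of the consequence is conditional. If 0.87 s is a between-group difference and participants hold steady, the hypothesis would be met about 1% of the time at an SD of change near 1.8 s, and at most 16% of the time across assumed SDs of 1 to 4 s. The 1.8 s value further assumes that 0.87 s and d = 0.48 share a contrast. The sample size and the planned test are unaffected. The point deserves correction because it changes what the study may conclude on this outcome and costs almost nothing to put right.

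**What to change.** 1. Check the source, reconcile the Literature Review with Study Hypotheses, and state which contrast 0.87 s and d = 0.48 each describe.
2. If the source reports 0.87 s as a change from baseline, keep it and correct the Literature Review.
3. Otherwise drop it. State the hypothesis as a mean reduction in sit-to-stand time from T1 to T3, which agrees with research question 3, assess it with the planned repeated measures analysis, and report the mean change with a confidence interval. A hypothesis of no worsening would not fit research question 3, which asks about improvement.
4. In either case delete p=0.01 from the hypothesis.

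Do not replace 0.87 s with a minimal detectable change derived from this study. Under Secondary Outcomes only the third stand is timed, and double rating lasts only until agreement is reached, so no repeat timings are planned from which test-retest error could be estimated.

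The cost is a few words and no new data. The downside is a less specific efficacy target if 0.87 s has to go.
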